## Abstract

**Background:**

Intimate partner violence (IPV) affects 2 in 5 women in Canada, leading to both physical and mental health consequences. Safety planning is a secondary prevention intervention designed to assist those experiencing IPV in taking steps to increase their safety and decrease contact with their abusive partner. Safety planning has been shown to help survivors mitigate the negative mental health effects of IPV and encourage actions to increase safety, but evaluation outside the United States remains limited.

**Objective:**

Our team plans to evaluate the use of single-case experimental design (SCED) to assess the effectiveness of a web-based safety planning app (*WITHWomen Pathways*) for women experiencing IPV in the Greater Toronto Area. The study also explores whether women can be safely engaged for intense follow-up.

**Methods:**

SCED evaluation will involve multiple baseline and postintervention assessments of a small number of women experiencing IPV (n=6). Participants will be recruited from IPV service organizations across the Greater Toronto Area. SCED will allow for rigorous within-subject comparison, using repeated measurements at multiple time points for 3 primary outcomes (decisional conflict, empowerment to take safety actions, and use of safety strategies) and 2 secondary outcomes (mental health and IPV recurrence). The evaluation will include 5 phases: recruitment, eligibility screening, multiple baseline interviews, intervention (web app delivery), and multiple postintervention assessments. In this paper, we also discuss the development of rigorous protocols for maintaining safety and flexible data collection methods (in person, via telephone, or online).

**Results:**

Recruitment began on July 3, 2024. As of December 2025, a total of 4 participants have been recruited and have completed multiple baseline assessments. Data analysis has been completed for 4 participants, and results are expected to be published in spring 2026.

**Conclusions:**

The SCED approach may offer a novel and ethical evaluation method for IPV interventions. If effective, the WITHWomen Pathways web app could significantly improve help-seeking and safety planning among women experiencing IPV in the GTA. This study may serve as a model for future IPV intervention evaluations, demonstrating robust evaluation data and participant safety.

## Introduction

Two in five women in Canada have experienced some form of intimate partner violence (IPV) in their lifetime [1]. Such experiences include aggressive, coercive, controlling, or abusive behaviors resulting in physical harm (eg, inflammatory conditions, self-harm, HIV, miscarriage, traumatic brain injuries) and nonphysical harm (eg, anxiety, posttraumatic stress disorder) [2-4]. While IPV occurs across populations and outside male-female relationships, the most widespread form of IPV is violence perpetrated against cisgender women by current or former cisgender male intimate partners [5,6].

 Although some women can extricate themselves from violent relationships on their own, most require assistance and support to either leave the relationship or work with the partner to end the violent behavior. Liang et al’s [7] theoretical framework of IPV help-seeking addresses 2 main forms: formal and informal. Formal help-seeking includes assistance from legal, medical, religious, or social services, while informal help-seeking refers to assistance sought from family, friends, other survivors, and trusted confidantes [7]. Both formal and informal help-seeking are shown to improve the mental health of those experiencing IPV, often by enhancing the survivor’s own coping abilities and social support [7].

 Safety planning is a secondary prevention intervention designed to empower survivors to begin the help-seeking process by taking independent actions to maximize their own safety. Similar to household safety plans for natural disasters or house fires, an IPV safety plan takes into consideration an individual’s available resources, living arrangements, and needs before recommending individualized, concrete actions that can prevent a violent event or mitigate its damage. To assist women experiencing IPV to begin the formal help-seeking process, this team created *WITHWomen Pathways,* a web-based safety planning app localized to the Greater Toronto Area (GTA; the metropolitan area encompassing Toronto, Ontario, Canada and the regional centers of Durham, Halton Peel, and York). This hyperlocal app is adapted from *MyPlan,* an existing safety planning mobile app in the United States [8] and Canada [9] that has shown effectiveness in reducing decisional conflict and promoting safety planning behaviors for women experiencing IPV in traditional randomized controlled trials (RCTs). Additional details on the creation of WITHWomen Pathways and its features are published elsewhere [10,11].

Safety planning interventions are commonly evaluated via their ability to jumpstart survivors’ help-seeking processes by (1) reducing decisional conflict (a state of uncertainty when faced with choices that represent loss or conflict with personal or cultural values), (2) empowering people who experience IPV to take actions to improve their safety, and (3) providing concrete, self-directed actions that align with their goals and needs [12-14]. While there is evidence from the United States to suggest that safety planning can help improve decisional conflict and mitigate future psychological and physical violence, there have been few evaluations of safety planning interventions outside the United States [9,14-16] and only 1 in Canada [17]. This review found no differences in depressive symptomatology or posttraumatic stress disorder symptoms between users of a static, generic safety planning app and one that is more tailored to their specific circumstances. However, the tailored app (which is more similar to the WITHWomen Pathways approach) did show meaningful effects on these mental health outcomes for subgroups of women—especially those who had children in the home, those who were experiencing more severe physical or sexual abuse, or those who lived in a large or medium-sized city [9]. The latter finding may be a function of the additional resources available to women in more urban areas, which a tailored app may be more helpful at recommending.

While evaluation of safety planning interventions is key to improving effectiveness and widespread implementation, RCTs in this space are exceedingly complex due to the important safety considerations and privacy concerns regarding women who are currently experiencing IPV [16-18]. Moreover, RCTs are expensive, complex studies that require large numbers of participants, and people experiencing IPV constitute a hard-to-reach population [19]. This places them out of reach for many community-based organizations that wish to evaluate innovative, survivor-centered programming but lack the scientific expertise and resources to conduct fully powered clinical trials. Moreover, many RCTs of safety planning interventions show null effects between intervention and control groups, which is hypothesized to be due (in part) to an intervention effect in the control group—that is, asking women in the control group about their IPV constitutes an intervention in and of itself, potentially blunting the true effect of the safety planning intervention [20,21].

Single-case experimental design (SCED) is a methodology that allows us to build on findings in a cost-effective and ethical way without unnecessary duplication via another large-scale, expensive RCT. As funding for research continues to decrease in many countries, such RCTs can be a drain on finite resources and impede scholarly progress [22,23]. To overcome some of the challenges posed by traditional evaluation methods, we are interested in using a potentially more rapid and efficient evaluation method that adapts the SCED clinical methodology, alongside novel safety protocols, to the evaluation of WITHWomen Pathways. SCED uses multiple observations in the same participant at short intervals (the time between observations depends on the outcome of interest) both before and after the introduction of the intervention (see Figure 1) [9,24]. Statistically nonsignificant differences in the outcome measures of interest between preintervention visits indicate stability and establish a preintervention baseline that is then compared to the subsequent postintervention time points [25-29]. After the intervention—which may be a single session or consist of multiple sessions [30,31]—is delivered, data collection over multiple postintervention time points allows for the establishment of behavioral trajectories that illustrate when and how change happens. In other words, the participant’s baseline measures act as the control. When multiple SCED cases are aggregated, SCED can explain small but meaningful causal variations in intervention effects using fewer participants than an RCT [28].

**Figure 1. F1:**
[figure not shown]
Overview of a typical single-case experimental design study flow.

SCED has been used in medical, psychological, and behavioral research for decades to better understand the mechanisms of intervention effects. Recently, it has also been used to assess the effectiveness of technology-based interventions in other areas [32], for example, in vulnerable populations such as adolescents experiencing psychological distress [33], individuals with serious mental illness [34,35], adults with severe autism spectrum disorder [36], and young children [37]. The extant literature suggests that SCED is a viable alternative to RCTs, especially for sensitive outcomes, because it allows for closer observation of individuals [38]—something which is critical for ensuring the immediate safety of participants living with IPV [26,27]. However, to the best of our knowledge, this will be the first adaptation of the methodology to IPV studies [32].

To gauge whether SCED is a viable approach for evaluating a web-based safety planning tool for English-speaking women in the GTA, we have established the following study objectives:

To understand whether women who are living with or have recently experienced IPV can be safely engaged for intense follow-up for the purpose of evaluating a safety planning interventionWe hypothesize that our safety protocols and individualized approach will allow for safe participation in the study, as measured by a lack of reportable or adverse events.To examine the preliminary effectiveness of WITHWomen Pathways and our novel safety protocols on 3 primary and 2 secondary outcomes of interestWe hypothesize that within-person changes to decisional conflict and depressive symptoms will show a decrease, whereas empowerment to take safety actions will demonstrate an increase.

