### Safely Contacting Participants

Safety protocols are of paramount importance in this study and necessitate bespoke approaches to safety strategies. To develop these strategies, we first consulted the literature and drafted a tentative protocol. These strategies include maintaining a general conversation during phone calls before discussing the research study until it is confirmed that the participant is in a safe environment, conducting regular check-ins to ensure the participant’s comfort and well-being, and sending an email prior to making phone calls to confirm that the scheduled time is still safe for the participant.

Our team’s peer advisory committee (comprising survivors and IPV advocates) provided feedback on the draft protocol and recommended changes to recruitment and contact procedures (eg, specifically mentioning IPV on recruitment flyers). During the consent process, participants will also be provided with an optional safe contact form where they can list up to 3 “safe contacts” who will only be contacted if the researcher cannot reach the participant. The purpose of this form will be communicated to participants as a standard procedure to ensure their safety if they cannot be reached. Safe contacts will be informed that the participant is part of a women’s health study and has given permission for the researcher to contact them if needed. Participants will be encouraged to inform their safe contacts about the possibility of being contacted by St Michael’s Hospital in the future. The participants will be asked to sign the safe contact form at baseline to ensure a thorough understanding and to provide written consent for contacting the listed individuals. Information requested for each safe contact includes name, relationship, phone number, and email. Participants will be asked to prioritize whom to contact first and to specify the preferred method of communication. The safe contact form will be reviewed and updated with participants at baseline and during follow-up to maintain accurate information.

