### Strategies to Prevent Attrition

Given the high participant burden of SCED and the potentially precarious position in which many women experiencing IPV find themselves, attrition from the study is likely. However, the research team has devised strategies to safely encourage participants to remain in the study. First, the study is designed to be as convenient for participants as possible, offering several modes of contact (in person, via telephone, and online), evening and weekend assessment options, and face-to-face interviews at partner organizations convenient to the participant. Compensation will also be given at the point of assessment, within a day following each check-in, and each assessment will be scheduled at the end of the preceding visit. For those who do not attend previously scheduled assessment visits, researchers will first reach out via the safe contact methods indicated by the participant at different times of the day. They will then search for updated information or attempt previously disconnected phone numbers before reaching out to the safe contacts listed by the participant. While resource limitations prevent us from overenrolling to guard against attrition, sample size is only one of several levers that SCED studies (as opposed to traditional evaluation designs) can use to improve statistical power. Should attrition become an issue, we will explore using additional baseline and follow-up measures in the remaining participants, simulating power using different effect size estimates, and assessing the number of outlier scores to understand its effect on generalizability [50].

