### Managing Minor Emotional Distress

Given the topic of IPV, study population, and sensitivity of the assessment questions, researchers will undergo training on how to handle situations where participants experience emotional distress during interviews. Sufficient time will be allocated during the initial interview to address any questions or concerns, including the potential for anxiety. For telephone or in-person surveys, researchers will help participants devise a step-by-step strategy to manage various scenarios, such as how to respond if they start crying or feel uncomfortable answering a question. Participants will also discuss options for managing anxiety during the interview ahead of time, such as deep breathing or temporarily discontinuing the interview. For online links, participants will be asked to complete the survey only when they are alone, and all participants will be provided with links to mental health resources at the end of the survey. The research coordinator will be in regular contact with all participants. Researchers will also note the PHQ-4 scores of all participants and those with elevated depressive and anxiety symptoms, making sure to carefully monitor these participants specifically and provide contact information for community mental health resources. Any adverse events beyond minor emotional distress will be immediately reported to the Research Ethics Board and integrated into our assessment of the safety of using SCED for IPV interventions.

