## Results

Recruitment commenced on July 3, 2024. As of December 2025, a total of 4 participants have completed the study. Data analysis has been completed for the 4 participants. Additional recruitment is underway, and results are expected to be published in spring 2026.

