### Study Limitations

There are some notable limitations to this study. First, research activities require that women be able to speak and read English, which excludes non-English speakers and women with visual impairment. Second, with its multiple points of intervention and smaller sample size, SCED has safety and statistical limitations. First, having multiple contact points with each participant increases the chance that the abusive partner could become aware of her participation, increasing the risk of IPV. To address this, we have developed strict safety protocols and can promptly leverage our connections with local service providers should emergencies arise. SCED approaches also have multiple measurements in close temporal proximity, increasing participant burden. To help limit attrition, we will clearly communicate with potential participants about the time involved at the outset; invest in training for study team members to promote friendly, empathetic connection with participants; and provide fair compensation for the demands on participants’ time. Statistically, SCED carries four major risks: (1) the potential for a lack of variability in the preintervention and postintervention measures because measurements are completed at short intervals, (2) limited generalizability due to a small number of cases, (3) threats to internal validity due to test bias and social desirability bias [40], and (4) potential confounding effects due to the lack of randomization. To address risk 1, we will use the WWC recommendations for conducting sensitivity analyses and reporting multiple effect size estimators (eg, multiple visual analysis methods). Regarding risk 2, although multiple-case SCED (when rigorously evaluated) can be generalizable in many of the same ways as RCTs, this necessitates replication, which requires additional resources [57]. We do not anticipate this preliminary trial to be generalizable. Rather, it is intended to better identify the potential utility of SCED protocols in the evaluation of IPV-related interventions and adaptations that may be necessary. Regarding risk 3, we will use the percentage of nonoverlapping data, corrected (PNDC), to ascertain patterns of preintervention increase, as recommended by the WWC (see Table 2). Regarding risk 4, once this preliminary trial is complete, we intend to introduce randomization to different permutations of the WITHWomen Pathways app in future studies.

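### Objective 1 measures safe engagement only by absence of reportable or adverse events in six women; it does not name IPV escalation, leaves loss of contact unclassified, and zero events would not exclude a per-woman risk of about 39%

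*Protocol article*

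**What the plan says.** The study objectives at the end of the Introduction state a single measure for Objective 1: the safety protocols and individualized approach "will allow for safe participation in the study, as measured by a lack of reportable or adverse events". No rate, denominator or acceptable risk is attached. The target is 6 women (Abstract, Methods; Eligibility Screening and Informed Consent). By the Results section, "As of December 2025, a total of 4 participants have completed the study".

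Other sections bear on how this measure would work:

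- **Hazard.** Study Limitations says that "having multiple contact points with each participant increases the chance that the abusive partner could become aware of her participation, increasing the risk of IPV".
- **Event reporting.** Under Managing Minor Emotional Distress, "Any adverse events beyond minor emotional distress will be immediately reported to the Research Ethics Board and integrated into our assessment" of safety. The article does not define an adverse event.
- **IPV data.** Table 1 lists the Composite Abuse Scale-Short Form as a secondary outcome. The Abstract says both secondary outcomes are measured repeatedly. Preintervention Assessments explains that IPV is secondary because it may well not change.
- **Exclusions.** Preintervention Assessments keeps women whose baseline never stabilizes out of the effectiveness evaluation, although they still receive the intervention.
- **Loss of contact.** Strategies to Prevent Attrition says "attrition from the study is likely" and that "resource limitations prevent us from overenrolling to guard against attrition". Missed visits lead to outreach and then to safe contacts, "who will only be contacted if the researcher cannot reach the participant"; the safe contact form is optional. Handling Missing Data deals only with interim missed assessments, for stability, plots and Tau-U.

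**The concern.** A measure based on the lack of events can only be as good as the capture of events. Three features weaken it here.

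First, the harm the article singles out, violence triggered by the partner learning of participation, is not named in the measure. The one instrument that would register a rise in abuse is assigned to Objective 2. It has no directional hypothesis there, and it drops out of the stated analysis for any woman with an unstable baseline.

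Second, a woman who disappears from contact contributes no event unless a tracing attempt uncovers one. Attrition therefore moves the result towards a favourable reading, and loss of contact is a situation in which harm is plausible.

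Third, six women are few for a conclusion from absence.

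What is at stake is the first objective and the closing suggestion in the Abstract that the study may be a model for later IPV evaluations, participant safety included. Followed as written, the criterion could return a finding of safe participation when harm was not reported or when a woman was never traced.

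**Working it through.** The article gives no event rate, threshold or power statement for Objective 1, so there is no planned figure to reproduce. The checks below use exact binomial arithmetic, treating women as independent with one yes/no event status each.

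**Inputs from the article:** n = 6 (target); 4 women completed by December 2025; attrition likely, rate not given; 5 to 8 baseline assessments, 1 intervention visit and 8 postintervention assessments.

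**Assumed for illustration, because the article gives no figure:** true per-woman risks of 5% to 30%; 1 to 3 women lost.

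**1. Upper limit with zero events in n women.** One-sided 95%: 1 − 0.05^(1/n). Two-sided 95%: 1 − 0.025^(1/n).

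| n followed | one-sided | two-sided |
|---|---|---|
| 6 | 39.3% | 45.9% |
| 5 | 45.1% | 52.2% |
| 4 | 52.7% | 60.2% |
| 3 | 63.2% | 70.8% |

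The row for n = 4 shows what zero events among the women completed so far would mean. The article does not report their event count.

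**2. Chance of seeing no event in 6 women,** (1 − p)^6: 73.5% if p = 5%, 53.1% if p = 10%, 26.2% if p = 20%, 11.8% if p = 30%.

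**3. Women needed, all event-free, for a one-sided 95% limit of at most u,** ln(0.05)/ln(1 − u) rounded up: 14 for u = 20%, 29 for u = 10%, 59 for u = 5%.

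**4. Loss of contact.** With no event among the women followed and d of 6 lost, the proportion with an event lies between 0/6 and d/6. The last column is the one-sided 95% Clopper-Pearson limit if every lost woman had an event.

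| lost (d) | best case | worst case | limit in worst case |
|---|---|---|---|
| 1 | 0% | 16.7% | 58.2% |
| 2 | 0% | 33.3% | 72.9% |
| 3 | 0% | 50.0% | 84.7% |

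**5. Could the existing data say more?** Planned contacts per woman are 5 + 1 + 8 = 14 to 8 + 1 + 8 = 17. IPV is to be measured at several of them. One caution: Preintervention Assessments says that only some of the measures are repeated at each baseline visit, so the article does not fix which visits carry the abuse scale.

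**The case against.** The strongest reply has four parts.

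*The article does not overclaim.* Objective 1 is worded as a hypothesis, Study Limitations calls the trial preliminary and does not expect it to generalize, and Research Plans foresees a further study before the app is integrated into services. This stands. A reader might infer that absence of events is offered as proof of safety; the text does not say so.

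*Lost women are not said to be event-free.* A reader might infer such a rule, but none is written. The article describes active tracing through preferred contact methods and up to three safe contacts, and both of its progress statements refer to 4 women, so no loss is documented so far. This also stands. What remains is that the form is optional, tracing can fail, and an absence-of-events measure gives an untraced woman no weight unless a rule says otherwise.

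*IPV is not excluded.* Violence brought on by participation could be reported as an adverse event and would then enter the safety assessment. The separate safety protocol, available on request, may define this. So it would be wrong to say that the plan leaves IPV out of safety. The narrower point holds: the stated measure does not name it and depends on someone reporting it, while a repeated abuse score goes unused for this purpose. It is also fair that a raw rise in score cannot be attributed to the study, since eligible women have current or recent IPV and there is no control group. That argues for descriptive use, not for a composite safety endpoint.

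*The limit of 39% is true of any six people.* Correct, and the article concedes its small sample. The concession is about generalizability, though, and does not say how the Objective 1 result will be qualified.

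**Conclusion.** The point holds in a limited form. Objective 1 rests on a single stated measure that does not name the hazard the article itself identifies, does not classify unresolved loss of contact, and carries no statement of uncertainty. Zero events in all 6 women would leave per-woman risks of up to 39% (one-sided) or 46% (two-sided) unexcluded. If 2 of the 6 were lost, an observed 0% would be compatible with 33%.

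The limits assume independent women and one event status per woman. The loss counts and true risks are illustrations. The documents do not support the harsher conclusion that the plan would declare a hazardous procedure safe: that would require IPV incidents to be kept out of adverse events and lost women to be coded as event-free, and neither is stated. The change is worth making because recruitment is still under way and the main data are already planned.

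**What to change.** Keep reportable and adverse events as the core of Objective 1, and add the following.

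1. Report for each woman any rise in Composite Abuse Scale score after enrolment as a descriptive safety measure, taking the first baseline assessment as reference because repeated contact starts there. Include women left out of the effectiveness evaluation for unstable baselines.
2. Show women with unresolved loss of contact as unknown, and give best-case and worst-case counts over all women enrolled.
3. Give the exact interval, and limit the conclusion to this form: no events seen among women followed; a risk of up to X% is not excluded.

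The cost is a change of wording and a few extra lines of reporting. The downside is a less favourable safety statement. Changes in background IPV also cannot be linked to participation unless a question on that is added, which would be new data collection. Logging code-word terminations and privacy breaches per contact would be informative, but it is optional and also new, since the article describes these as protective procedures and does not say they are recorded.
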